#### Recruitment

Based on the yearly caseload of patients with TKA in the study center, we anticipate a recruitment phase of 24 months. In the first 12 months participants receive the standard consent form (12 months pre-phase). After this period, the evidence-based consent form will be introduced and subsequent participants will receive the evidence-based consent form (12 months post-phase). Recruitment is expected to start in March 2021 and finish in February 2023. Study participants will be recruited by study nurses or physicians during the office hours of the clinic for orthopedics, trauma surgery, and sports traumatology of the Cologne-Merheim hospital. There will be no financial incentives for participation.

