#### Statistical model

We will report baseline characteristics of the study population and outcomes descriptively.

We will use an ITS analysis to determine level and slope changes after the implementation of the evidence-based informed consent forms. We will use segmented regression models for our analysis. The basic model is *Y*_*t*_ = *β*_0_ + *β*_1_*T*_*t*_ + *β*_2_*X*_*t*_ + *β*_3_(*T* − *T*_0_)*X*_*t*_

*X*_t_ is a dummy which differentiates pre- and post-intervention periods. *T* is the time since the start of the study in months. β_0_ is the base level. β_1_ is the course of the slope before the implementation of the intervention. β_2_ is the level change, which describes the immediate effect on *Y* after the implementation of intervention *X*. β_3_ is the course of the slope after the implementation of the intervention, whereby *T*_o_ is the time of beginning of the study. We will use negative-binomial regression models for all count data (nocebo effect and objective knowledge questions) and generalized linear model for outcomes which can be analyzed as continuous variables (anxiety, satisfaction, quality of life, OKS).

We will create two models. One model will analyze the intervention as a complex package of measures on hospital level. The intervention effect will be analyzed on the hospital level. We will adjust the analysis for potential unforeseen time-varying confounders (e.g., changes of the standard consent form by hospital information policies, structural changes in consent because of corona pandemic). Potential confounders for each outcome will be identified based on visual inspection of trajectory curve and content-related thinking. We will assess autocorrelation by examining the plot of residuals.

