In a second model, we will analyze the intervention effect on an individual level. This means, the study is analyzed as historical cohort study. In this model, the individual intervention components (informed consent forms, parallel performance of informed consent by orthopedic and aesthetic medical staff, participation on the training for evidence-based decision-making) are modelled as separate intervention components. We will perform this exploratory analysis to get insights into the isolated effect of evidence-based informed consent forms and interaction effects with other intervention components. We will adjust the models for baseline characteristics (age, sex, educational level, and marital status) and a potential time trend (since the comparison group is a historical control).

In case > 5% of data for an outcome are missing, we will impute the missing data by multiple imputation using the Markov chain Monte Carlo method. In addition to this primary analysis, we will perform a best-case/worst-case analysis to assess the robustness of results depending on missing data [48].

To quantify the statistical uncertainty, the associated 95% confidence intervals will be provided for all effect estimates. As we will conduct an explorative pilot study, we will not perform a test for statistically significant differences. We will prepare interrupted-time-series graphs to visualize the results [49].

All analyses will be performed using SAS software [50] and R [51].

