## Limitations

The study was planned as a non-randomized study and is therefore at risk for confounding bias. Moreover, this is a time series study which might be biased by temporal effects. The risk of temporal changes is in particular high because of the dynamic COVID-19 pandemic (e.g., hospital limits surgery to patients with acute pain). A randomized controlled trial would control for unmeasured confounding. However, we decided against a randomization on individual level because we anticipated that there is a high risk of bias due to contamination. The study was not planned as a cluster-randomized trial because this would have exaggerated the expense for a pilot-trial.

Finally, external validity might be limited because the study is only performed in one hospital in Germany.

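### With two adjacent March-to-February years and no seasonal term, a stable annual cycle would enter the level change β2 at up to 1.95 times its amplitude

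*Protocol article*

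**What the plan says.** Under Recruitment, the article plans two consecutive phases: "Recruitment is expected to start in March 2021 and finish in February 2023". On the pre-phase it says "In the first 12 months participants receive the standard consent form (12 months pre-phase"; after the change of forms, "subsequent participants will receive the evidence-based consent form (12 months post-phase". Each phase therefore runs from March to February.

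Under Statistical model it says "We will use segmented regression models for our analysis". The basic model has an intercept, linear time, a post-period dummy X and a time-by-X term. T "is the time since the start of the study in months", and β2 "is the level change, which describes the immediate effect on" the outcome. T0 is defined as the beginning of the study. A second model, at the individual level, adjusts for patient characteristics and "a potential time trend (since the comparison group is a historical control".

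The same section allows adjustment for time-varying confounders that it calls unforeseen. They are to be chosen for each outcome by looking at the trajectory and by subject-matter reasoning; the examples are consent policy and pandemic changes. Under Limitations the article accepts that time effects may bias the study and adds: "The risk of temporal changes is in particular high because of the dynamic COVID-19 pandemic". Season is not named in any of these places.

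**The concern.** Matching calendar years looks like protection against season, and for a simple comparison of the two phase means it is. The planned models fit a line through time. Over one March-to-February year, an annual cycle has a non-zero least-squares slope for almost any peak time. Both segments then carry the same false slope, and two parallel sloping lines with equal means must be separated by a jump at the switch. That jump is read as β2.

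The study plans no significance tests, so its results are the estimates and their confidence intervals. A definitive cluster-randomized trial is planned if the pilot indicates positive effects. A level change created or hidden by season could influence that decision.

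**Working it through.** **Inputs.** From Recruitment: 12 + 12 months, March to February. From Statistical model: terms 1, T, X and (T − T0)X, with T in months. From Sample size: 220 enrolled, 10% dropout, 220 × 0.9 = 198 analysed. The section's own detection figure reproduces: 1 − 0.98^198 = 0.982, stated as 98%. The plan gives no figure on season. Assumed here: one stable annual sinusoid A·cos(2π(t − φ)/12), no true effect, even recruitment (198/24 = 8.25 patients per month), identity link and residual SD 1.

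**1. False slope within one segment.** For 12 equally spaced months, Σ(t − t̄)² = 12 × (144 − 1)/12 = 143. The largest value of Σ(t − t̄)cos(2π(t − φ)/12) over φ is 12/(2 sin 15°) = 23.18. The worst-case slope is 23.18/143 = 0.1621·A per month.

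**2. Effect on the model terms.** The second segment covers the same calendar months, so it has the same slope and the same mean (zero).
- β3: 0.
- Plain post-minus-pre mean difference: 0.
- β2: the segment midpoints are 12 months apart, so the lines are separated by 12 × 0.1621 = **1.945·A** in the worst case.

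Because the slopes are equal, the result is the same for T0 at the study start or at the switch. It is also the same for a step plus one common linear trend, which is the form of time adjustment in the individual-level model.

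**3. Dependence on the peak month (mid-month).**

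| Peak | Loading on β2 |
|---|---|
| May, June | +1.88 |
| April, July | +1.38 |
| March, August | +0.50 |
| September, February | −0.50 |
| October, January | −1.38 |
| November, December | −1.88 |

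The mean absolute loading over all phases is (2/π) × 1.945 = 1.24.

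**4. Size.** The amplitude is not in the documents. For an assumed A of 0, 0.1 and 0.3 SD, the worst-case false level change is 0, 0.19 and 0.58 SD.

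**5. Random error of β2.**
- T0 at the switch: variance = 2 × (1/12 + 6²/143)/8.25 = 0.0812; SE 0.285; 95% half-width 1.96 × 0.285 = 0.56 SD.
- T0 at the study start, as written: variance = [(1/12 + 6²/143) + (1/12 + 18²/143)]/8.25 = 0.325; SE 0.570; half-width 1.12 SD.

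**6. With one sine/cosine pair.** The seasonal loading on β2 becomes 0. Its SE (T0 at the switch) rises from 0.285 to 0.428, a ratio of 1.50. The SE of β3 does not change.

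**7. Variants.** Continuous even recruitment gives a maximum of 1.91. Table 1 shows a 25-month study period with an interruption column. If that means a one-month gap between the phases, the maximum is 2.04, and β3 then also picks up as much as 0.084·A per month.

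**The case against.** The strongest reply is that the article prints only a basic model and then provides for adjustment for time-varying confounders, and that harmonic terms are the kind of detail an analysis plan supplies. It also concedes temporal bias openly. Part of this stands: the plan does not exclude a seasonal term, and one may be specified in a document not shown. But the clause covers unforeseen influences found by inspecting the curve, and season is foreseeable. Inspection is also a weak safeguard. With 8.25 patients a month, a monthly mean has an SE of 1/√8.25 = 0.35 SD, larger than the assumed cycle.

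A second reply is that nothing quoted is false: the article never claims that the two years balance season, and matched calendar years are a sensible layout. That is correct. The weakness comes from combining the calendar with a linear-trend model.

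A reader might also infer that the study is set up to show a false benefit from a winter peak in its main estimate. The documents do not support this:
- They give no seasonal amplitude and no peak month for any outcome. A May or June peak would push β2 the other way.
- They do not make β2 the main effect. Level and slope changes are both targets, and β3 is free of this bias on the 24-month calendar.
- The closeness of the worst-case bias (0.58 SD) to the CI half-width (0.56 SD) depends on an assumed amplitude and on placing T0 at the switch. With T0 as written, the half-width is 1.12 SD.

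**Conclusion.** The point holds as a conditional one. On the stated calendar, the models as written leave β2 exposed to a stable annual cycle at up to 1.95 times its amplitude, about 1.24 times on average, with the sign set by the peak month. β3 and the plain mean difference are not exposed. The real bias may be nil. At an assumed amplitude of 0 to 0.3 SD it is 0 to about 0.58 SD.

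The result assumes one sinusoid repeating in both years, even recruitment and an identity link. For the negative-binomial outcomes it applies approximately on the log scale. For the individual-level model it was worked for a step plus a linear trend, without separate intervention components. Because this is an exploratory pilot without tests, the consequence is a possibly misleading estimate and interval; no claim about type I error follows. It is a point to consider, not a defect that invalidates the design.

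**What to change.** Name season as a pre-specified time-varying confounder. Beside each time-trend model, report two sensitivity analyses:

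1. The same model with one annual sine/cosine pair added.
2. The calendar-month-matched difference: each post-phase month minus the same month a year earlier, averaged. A stable annual cycle cancels.

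State in advance that a level change whose point estimate differs clearly between these analyses will be interpreted with caution. It should not be ruled out on that ground, because both checks have weaknesses of their own.

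The cost is a few lines of analysis plan and no new data. The harmonic model uses six parameters on 24 monthly points and has about a 1.5-fold larger SE for β2 (T0 at the switch). The matched difference does not remove a long-term trend. Both therefore belong beside the planned models and do not replace them.

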### Participant timeline

Table 1 depicts the participant timeline. The study includes a pre-interruption and post-interruption-phase. Participants in the pre-phase will receive informed consent based on standard consent forms (control) while participants in the post-phase will receive informed consent based on the newly developed evidence-based consent forms (intervention). Irrespective of the phase, all participating patients will follow the same study flow: study enrollment of each patient will take place approximately 4 weeks before surgery. They will receive informed consent procedures for TKA approximately 2–4 days before surgery. The informed consent procedure for anesthesia takes place approximately 4 weeks or 2–4 days before surgery, depending on the patients’ morbidity and the flexibility in scheduling. Outcomes will be measured at four specific time points for each patient: at the day of enrollment, 1 day before surgery, 3 days and 30 days after discharge from hospital.

**Table 1 Tab1:** Participant timeline (SPIRIT figure)

	Study period (25 months)													
		Pre-phase						Interruption	Post-phase					
	Time-point	4 weeks before surgery	2–4 days before surgery	1 day before surgery	Surgery	3 days after discharge	30 days after discharge		4 weeks before surgery	2–4 day before surgery	1 day before surgery	Surgery	3 days after discharge	30 days after discharge
**Enrolment**	**Eligibility screen**	X							X					
	**Informed consent**	X							X					
**Control**	**Standard consent form anesthesia**	X^a^	X^a^											
	**Standard consent form TKA**		X											
**Intervention**	**Evidence-based consent form anesthesia**								X^a^	X^a^				
	**Evidence-based consent form TKA**									X				
	**Surgery**				X							X		
**Assessments**	**Patient characteristics**	X							X					
	**Baseline anxiety**	X							X					
	**Anxiety**			X							X			
	**Health knowledge**			X							X			
	**Satisfaction with physician-patient-communication**			X							X			
	**Nocebo-effect**					X							X	
	**Quality of Life**						X							X
	**Pain and function**						X							X

^a^Informed consent for anesthesia takes place approximately 4 weeks or 2–4 days before surgery, depending on the patients’ morbidity and the flexibility in scheduling

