#### Outcomes and measurement instruments

We plan to measure the following patient-relevant outcomes:
Primary outcomes:Anxiety: subjective fear/anxiety of adverse events possibly caused by surgery or anesthesia
○ Measuring instrument: numeric rating scale 0–10 (validation see [38, 39]) and surgical fear questionnaire (SFQ) [40]. The SFQ comprises 8 items reflecting different aspects of surgery-related fear (e.g., anesthesia or side effects). All items are scored on a numeric rating scale 0–10. It is validated in adult patients scheduled for an elective surgery.○ Measure: meanNocebo-effect: patient reported adverse events (e.g., headache after anesthesia)
○ Measuring instrument: a questionnaire will be developed. We will use closed simple-choice questions (yes/no) to detect frequent adverse events and open-ended questions to detect other (less common) adverse events.○ Measure: proportion of patients with complications or adverse eventsSecondary outcomes:Knowledge or risk perception: questions for knowledge about benefits and risks
○ Measuring instrument: objective knowledge questions (e.g., correct risk assessment) derived in the development phase. The development will be based on previous experiences with the measure of informed choice [33, 34].○ Measure: proportion of correctly answered questionsSatisfaction with the physician-patient-communication and informed consent form
○ Measuring instrument: numeric rating scale 0–10 (validation see [41])○ Measure: meanQuality of life (QoL)
○ Measuring instrument: numeric rating scale 0–100 (validation see [42])○ Measure: meanPain and function
○ Measuring instrument: Oxford Knee Score (OKS) [43]. The OKS is a 12-item questionnaire with five scoring categories (validation see [43]).○ Measure: mean

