### Methods: data collection, management, and analysis

#### Data collection and management

We will collect the participants’ characteristics (e.g., education) using patient surveys as standardized in German socio economic panels [45]. All outcomes will be collected with standardized patient surveys. All patient surveys will be performed by the same four interviewers based on an interviewer manual to ensure consistency.

Data will be collected using an electronic case report form (eCRF) and stored in an electronic data management system (REDCap) [46, 47]. The eCRF and data management system will be piloted with dummy participants (hypothetical patients). We will perform a sample of double data entry to prove data quality. Only authorized study personal will have access to the data management system.

To ensure high retention, the participants’ expenditure of time for study participation will be kept as low as possible. Moreover, due to the nature of the intervention, there will be no physical strain for the participants caused by study participation.

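### OKS and quality of life have no pre-operative value, so an abrupt, temporary or non-linear shift in case mix cannot be separated from the effect of the intervention package

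*Protocol article*

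**What the plan says.** The text under Participant timeline lists four measurement occasions without saying which outcome belongs to which: "Outcomes will be measured at four specific time points for each patient: at the day of enrollment", followed by the eve of surgery and two contacts after the hospital stay. Table 1 allocates them:

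- "Baseline anxiety" and patient characteristics are marked about four weeks before surgery.
- "Quality of Life" and "Pain and function" each have one mark per phase, 30 days after discharge, and none before surgery.

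Both are secondary outcomes summarised as a mean. For pain and function, the outcome list gives: "Measuring instrument: Oxford Knee Score (OKS) [43]. The OKS is a 12-item questionnaire with five scoring categories". Quality of life is a 0–100 numeric rating scale.

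On covariates, Data collection and management says: "We will collect the participants’ characteristics (e.g., education) using patient surveys as standardized in German socio economic panels". Under Statistical model, the individual-level model adjusts for age, sex, education, marital status and a time trend. The hospital-level segmented model has a pre-period slope and allows adjustment for time-varying confounders, chosen for each outcome from the trajectory plot and subject-matter reasoning. Neither names pre-operative pain, function or quality of life.

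Limitations states that the study is non-randomised and open to confounding and temporal bias. Its example is "hospital limits surgery to patients with acute pain".

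**The concern.** Pre-operative pain and function are natural predictors of pain and function one month after surgery. Without randomisation, nothing makes the two phases alike in this respect. The article's own example of a temporal change, selecting patients for surgery by pain, acts directly on what the OKS measures. With no pre-operative score, the analyst can neither see whether such a shift happened nor adjust for it at patient level. No later analysis plan can recover a value that was never collected.

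At stake are the estimates for the two health outcomes at the end of the logic model. The pilot is also meant to supply the data basis for sizing a definitive trial. Without baseline scores it cannot provide the baseline-to-follow-up correlation needed to plan a baseline-adjusted analysis of these outcomes.

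**Working it through.** The article gives no figure on this point. Its sample-size figure reproduces and is not in dispute: 220 × 0.9 = 198 analysed, and 1 − 0.98^198 = 0.982 against the stated 98%. It supplies 198/2 = 99 patients per phase for step 3.

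**Step 1: which shifts reach the estimate.** Inputs are 12 monthly points per phase (Recruitment) and the segmented model under Statistical model. The slope-change term is centred at the switch, so that β2 is the immediate change, as the article describes it. Let a one-unit pre-operative shift pass in full into the 30-day score, without noise.

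- Step at the switch: level change 1.00, slope change 0.
- Linear drift over 24 months, phase means differing by 1: level change 0.00, slope change 0.00.
- Shift in the last 3 pre-phase months only: the pre-phase mean is 3/12 = 0.25. With months at 0.5 to 11.5, the squared deviations from 6 sum to 143, so the fitted slope is (3.5 + 4.5 + 5.5)/143 = 0.0944. The fitted value at the switch is 0.25 + 6 × 0.0944 = 0.82. Level change −0.82, slope change −0.09 per month.
- Shift in the first 3 post-phase months only: the mirror image. Level change +0.82, slope change −0.09 per month.
- Shift over 3 months on each side: level change 0.82 − 0.82 = 0.00, slope change −2 × 0.0944 = −0.19 per month.

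In the third and fourth patterns the phase means differ by only 0.25, yet the level change moves by 0.82. The fitted trends magnify a short disturbance next to the switch. (The article defines T0 as the start of the study. Coded literally, β2 is no longer the change at the switch. The step and linear-drift results stay the same, but β2 for the temporary shifts differs. That is a separate matter.)

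**Step 2: size of the bias.** Only part of a baseline shift carries over to 30 days. Let d be the shift in baseline SDs and r the standardised baseline-to-30-day slope, which is the correlation. The documents give neither, so both are assumed: d = 0.2 to 0.5, r = 0.3 to 0.7.

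- Step at the switch: r·d = 0.3 × 0.2 = 0.06 SD to 0.7 × 0.5 = 0.35 SD.
- Three-month shift on one side: 0.82 × r·d = 0.05 to 0.29 SD.
- Linear drift: about 0.

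**Step 3: against the precision available.** With 99 per phase and outcome SD 1:

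- Crude difference: SE = √(2/99) = 0.142, 95% half-width 1.96 × 0.142 = 0.28 SD.
- Segmented level change, patients spread evenly over time: SE = 0.282, half-width 1.96 × 0.282 = 0.55 SD.

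The top of the step-shift range exceeds the first half-width but not the second.

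**Step 4: precision gained by adjusting.** Residual variance falls to 1 − r²: 0.91 at r = 0.3 and 0.51 at r = 0.7. The SE falls by the factor √(1 − r²), 0.95 and 0.71, a reduction of about 5% to 29%.

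**The case against.** The primary analysis is not a crude pre/post contrast. It fits a pre-period slope, the individual-level model includes a time trend, and hospital-level adjustment for time-varying events is foreseen, with a pandemic example. A restriction on surgery can be dated. The limitations are disclosed, the outcomes are secondary, no significance tests are planned, and effectiveness is left to a later cluster-randomised trial. The article also aims to keep participants' time low, and its list of patient characteristics is introduced as an example, so a severity item could exist.

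Much of this stands. A reader might infer that any difference between phases in pre-operative pain would be read as an effect of the form. The documents do not support that, because a steady linear drift leaves both coefficients at zero and the hospital-level model estimates the whole package, not the form alone. Nor does the article predict the bias: it names a possible one and gives an example. It is also wrong to say that no adjustment is planned.

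What does not stand is that the planned adjustment suffices. A dated indicator for a restriction does not measure who was operated on, and one that coincides with the switch cannot be separated from the intervention dummy. The individual-level model, which the article itself treats as a historical cohort analysis, depends on measured baseline covariates, and its named list is sociodemographic. The general admission of confounding does not mention the missing baseline.

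**Conclusion.** The concern holds for abrupt, temporary or non-linear shifts in pre-operative pain or function, and not for a steady drift. For a step at the switch the level change is biased by about r·d, here 0.06 to 0.35 SD. For a three-month disturbance next to the switch it is about 0.82 of that. One straddling the switch affects the slope change instead. These figures rest on assumed d and r and on the stylised patterns above. Nothing in the documents shows that a shift occurred or how large it would be.

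The bias would usually be smaller than the uncertainty of the segmented estimate, and it touches two secondary outcomes of an exploratory pilot, so it does not undermine the study. It is still worth correcting, because the missing value is cheap to collect.

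The sentence on four time points should not be read as giving these outcomes a baseline, since Table 1 marks only anxiety among the outcomes at enrolment. The two places should agree.

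**What to change.** - Ask the 12-item OKS and the 0–100 quality-of-life scale at the existing enrolment interview in both phases, and mark this in Table 1. Since anaesthesia consent may also take place about four weeks before surgery, ask these items before any consent form is discussed.
- In the individual-level OKS and quality-of-life models, add the patient's baseline value as a covariate.
- In the hospital-level model, add the monthly mean baseline value of the patients analysed as a time-varying covariate. This takes the model from four coefficients to five, on 24 monthly points.
- State in the Participant timeline text which outcomes are measured at which occasion.
- If baseline collection is no longer possible in both phases, report these two outcomes as descriptive only and name the missing baseline under Limitations.

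The cost is 12 + 1 = 13 more items at a contact that already takes place, and slightly more patient time, against the stated aim of keeping that time low to protect retention.
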